#### Secondary Analyses

Secondary analyses will be conducted. (1) Analytic methods described in the primary aims will be repeated but applied to secondary measures of sleep disturbance and well-being outcomes as described in the Secondary Outcomes section. (2) Analytic methods described in the primary aims will be repeated but applied to outcome measures collected at week 56. (3) Sparse unsupervised clustering and principal component analysis analyses will be used to identify cohesive factors of dysfunction in sleep complaints and patterns of mental health outcomes at baseline. Regression models will be used to quantify the relationships within and between sleep complaints and patterns of mental health outcomes. (4) Age and sex differences in treatment response and as moderators of relationships between sleep complaints, insomnia risk factors, and mental health outcomes will be explored.

### Ethics Approval and Trial Registration

The IRB of Stanford University (Stanford, CA) approved the study, which is performed following the rules of the seventh edition (2013) of the Declaration of Helsinki (IRB-55940). It received initial approval from the IRB on April 30, 2020.

## Results

### Trial Status and Timeline

The trial began recruitment on June 4, 2020, and the first participant was consented on June 10, 2020. As of October 2021, 794 subjects had completed prescreening, and 96 subjects had completed a Zoom screening session. A total of 49 participants were randomized to a study group (26 to the CBT-I group and 23 to the waitlist control group). Overall, 38 participants had completed the week 6 follow-up, 37 had completed the week 12 follow-up, 34 had completed the week 28 follow-up, and 15 had completed the week 56 follow-up. At the time of this writing, there were an additional 3 participants awaiting the 28-week follow-up and a total of 23 participants awaiting the week 56 follow-up (13 in CBT-I and 10 in waitlist control group). The study closed to enrollment of new subjects on June 17, 2021. As of the writing of this paper, due to the outstanding data collection of the remaining 28- and 56-week data, we had conducted interim analyses for the week 6 follow-up but had not tested the results of our primary hypotheses in full. We expect primary results of the study to be published in 2022.

## Discussion

Here, we outline the protocol of an innovative research project responding to the mental health crisis related to the COVID-19 pandemic. We aim to address several gaps in the literature by investigating the use of an early, brief, nonpharmacological insomnia intervention delivered via telehealth to treat insomnia symptoms arising during a stressful life event and prevent worsening insomnia or mental health outcomes. This study represents multiple levels of innovation. First, to the best of our knowledge, this is the only project clinically responding to the large-scale increase in sleep disturbance during the COVID-19 pandemic. Although many studies are documenting the robust changes in sleep during the pandemic, this project is the first to test an intervention and examine pandemic-related predictors of intervention response. Second, on a broader scale, this is one of only a few studies testing the prospective temporal relationship between sleep disturbance and well-being. Lastly, to our knowledge, this is the only study of early deployment of CBT-I to treat insomnia symptoms arising from a stressful global event.

This study was conceived and launched in response to the global pandemic of COVID-19, which, while rendering it novel, presents unique challenges. First, to address our scientific questions, we sought to recruit participants early in the course of their sleep disturbance, causing a significant urgency to launch the study. This time pressure led us to conduct this study with limited resources, which impacted our recruitment efforts. We were unable to offer compensation for participation. We relied heavily on recruiting participants through free online platforms, such as social media posts, online message boards, and electronic newsletters. Due to these recruitment concerns and the resulting decreased statistical power for the planned analysis, we view this as a feasibility study. Therefore, the planned analyses and publications resulting from this protocol will utilize effect size estimates, rather than statistical significance, to provide pilot and feasibility data to inform future hypotheses. A second potential limitation is the unequal attrition rate in the treatment versus the waitlist control group. Since participants are not financially compensated, the primary motivation of participation is meeting with a therapist on a weekly basis to address their sleep concerns. Thus, it is possible that individuals in the waitlist control group were more likely to decline to participate in follow-up time points due to loss of interest or spontaneous improvement in symptoms over time. Although this could potentially affect the ability to detect significant differences in between-group comparisons at the long-term follow-up time points due to inadequate power, our analytic approach using regression models has the advantage of increased efficiency and power over unadjusted analyses [63,64]. We will address this issue by assessing whether missingness is related to any observed covariates. If this is the case, an issue of greater concern is the potential bias in the estimate of the treatment effect if neither the missing completely at random (MCAR) nor the missing at random (MAR) assumption holds. Although mixed effects linear models lead to unbiased estimates of the treatment effect under the MCAR and MAR assumptions, estimates may be biased under nonignorable missingness. Further sensitivity analyses will be performed if this is the case.

Although the unique conditions created by the COVID-19 pandemic posed many novel challenges, it also raises the potential significance of this protocol and feasibility study: It is unlikely that we or another group will be able to replicate this study in the future. Therefore, although the sample will be smaller than nonpandemic trials, it will likely be the largest sample to report on a sleep intervention deployed during the acute stage of a global pandemic. Supporting our hypothesis, the findings of a recent, large-scale clinical trial indicate that treatment of insomnia with CBT-I has an overall benefit in the prevention of incidence and recurrence of major depression in older adults with insomnia disorder. However, this trial utilized an in-person intervention in subjects with chronic insomnia [65]. Our study remains important by extending these findings to address the public health need for an effective, remote intervention to treat insomnia early and potentially prevent negative well-being outcomes. This project will lay the groundwork for future studies investigating early deployment of CBT-I to treat insomnia precipitated by a stressful event and whether this prevents adverse mental health outcomes for which poor sleep is a risk factor. Further, our investigation of pandemic-related risk factors for insomnia could guide future hypotheses for studies conducted in nonpandemic conditions.

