#### Power Calculation

Due to the anticipated difficulties in recruitment that will likely arise from the complexities of running a study during a pandemic and the time-sensitive nature of implementing an early sleep intervention relative to both the start of the pandemic and insomnia symptoms, we view this trial as a feasibility study. Therefore, for this feasibility trial, we aimed to recruit a total of 50 subjects, which would result in 25 subjects in each study group. With this sample size, our power calculations were derived using the 2-group *t* test of equal means based on the difference between CBT-I and waitlist control group at 28 weeks, at a 5% level of significance. With 25 per group, the study is 80% powered to detect a large effect size (Cohen d=0.80).

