#### Primary Outcomes

Primary outcomes of insomnia, well-being, and predictors of treatment response are collected at baseline (week 0), weeks 6, 12, 28, and 56. Primary outcomes of insomnia (ISI) and well-being were also collected at weeks 1-5. The primary time points are weeks 6, 12, and 28.

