#### Primary Analyses

Statistical analyses aim 1 is to determine whether a brief, telehealth CBT-I reduces insomnia symptoms arising during the COVID-19 pandemic. All primary analyses will be performed using the intention-to-treat principle. We will test whether CBT-I is superior to a waitlist control in reducing insomnia symptoms by using a mixed effects linear model with autoregressive error structure using intention-to-treat analysis with outcomes at time points 6, 12, and 28. Insomnia severity as measured by the ISI will be entered as the dependent variable with randomization group (2 levels), time point (weeks 0, 6, 12, and 28), and group-by-time interaction included as fixed effects. The model will also include a random slope. Several hypotheses (1.1a-d) will be tested using the described mixed effects model.

Hypothesis 1.1a is that individuals assigned to the CBT-I group will experience an improved trajectory of insomnia symptoms during the waitlist-controlled 28-week period relative to those assigned to the waitlist control group. This hypothesis will be tested using a likelihood ratio test of the coefficients of the time and group-by-time interaction of the aforementioned mixed effects linear model.

Hypotheses 1.1b-1.1d are that individuals assigned to the CBT-I group during the waitlist-controlled period will have lower insomnia symptoms compared with those assigned to the waitlist-control group immediately posttreatment (hypothesis 1.1b; week 6) and at the short-term (hypothesis 1.1c; week 12) and long-term (hypothesis 1.1d; week 28) follow-ups. These hypotheses will be tested using the aforementioned mixed effects linear model with independent likelihood ratio tests using the treatment coefficient for the posttreatment (hypothesis 1.1b; Δ_1_ in Figure 2), short-term (hypothesis 1.1c; Δ_2_ in Figure 2), and long-term (hypothesis 1.1c; Δ_3_ in Figure 2) follow-up time points.

We will also test whether CBT-I is superior to the waitlist control in preventing an insomnia diagnosis following treatment by using multiple logistic regression analysis.

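### The missing-data sensitivity analysis hangs on a condition that cannot show when it is needed, and the aim 1 ISI model leaves out weekly scores collected before most losses

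*Protocol article*

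**What the plan says.** The Discussion expects attrition to differ between arms. It offers this, with a hedge, as one explanation: "individuals in the waitlist control group were more likely to decline to participate in follow-up time points due to loss of interest or spontaneous improvement". It then says "We will address this issue by assessing whether missingness is related to any observed covariates". The next sentences warn of bias if neither MCAR nor MAR holds, and note that mixed models are unbiased under those two assumptions but may be biased under nonignorable missingness. The passage closes with "Further sensitivity analyses will be performed if this is the case". No sensitivity analysis is promised outside that condition.

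On the data used, Primary Outcomes states: "Primary outcomes of insomnia (ISI) and well-being were also collected at weeks 1-5". Primary Analyses specifies the aim 1 mixed model "using intention-to-treat analysis with outcomes at time points 6, 12, and 28", and the time factor has the levels 0, 6, 12 and 28. Weeks 1-5 are not in it.

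On follow-up, Trial Status and Timeline reports 49 randomised (26 CBT-I, 23 waitlist). Of these, "38 participants had completed the week 6 follow-up", 37 had completed week 12 and 34 had completed week 28, with 3 still awaiting week 28.

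**The concern.** A sensitivity analysis for nonignorable dropout asks how far the result depends on an assumption that the data cannot check. Making it conditional on a finding in the data defeats that purpose. An association between missingness and observed covariates is evidence against MCAR. It neither shows nor excludes MNAR.

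The ISI model adds to the problem. A likelihood-based mixed model protects against dropout only through the outcomes and covariates it contains. Someone who leaves between weeks 1 and 6 has weekly ISI scores showing whether they were improving, but the aim 1 model sees only their baseline score.

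At stake is the estimate itself. The Statistical Procedure section and the Discussion both put effect sizes and intervals ahead of significance. If waitlist participants who improved are the ones who leave, and the model does not capture that improvement, the remaining waitlist mean ISI is too high and CBT-I looks better than it is.

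**Working it through.** **The plan's own figure.** Power Calculation states "With 25 per group, the study is 80% powered to detect a large effect size (Cohen d=0.80"), "at a 5% level of significance". The noncentrality is 0.80 × √(25×25/50) = 2.83. The normal approximation gives Φ(2.83 − 1.96) = 0.807, and the two-sided t test on 48 degrees of freedom gives 0.791. The stated 80% is reproduced. The point here concerns bias, not this figure.

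**How much is missing, and when** (Trial Status and Timeline):
- Week 6: 49 − 38 = 11; 11/49 = 22.4%.
- Week 12: 49 − 37 = 12; 12/49 = 24.5%.
- Week 28: 49 − (34 + 3) = 12, or 24.5%, if all 3 pending complete; 49 − 34 = 15, or 30.6%, if none do.

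In net terms, 11 of the 12 losses at week 12 are already present at week 6. Unless they return, these people have no post-baseline ISI in the aim 1 model.

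**The trigger under each reading:**
- *This* means that missingness is related to covariates. Such a link can exist under MAR, where a mixed model containing those covariates is already valid, and can be absent under MNAR.
- *This* means that missingness is nonignorable. No observed data can establish that, so the condition can never be declared met.

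**How the first reading behaves at this size.** The article gives no threshold, so p < 0.05 is assumed. In a simulation with 26 and 23 participants, testing arm, sex and baseline ISI, the check fired in about 12% of trials when dropout depended on unobserved later change with no covariate link. It fired in about 90% when dropout depended only on baseline ISI, which is MAR. If arm counts as a covariate and true dropout is 36% (waitlist) against 12% (CBT-I), Fisher's exact test at 5% detects the imbalance in 44% of trials. At 30% against 20% it does so in 9%. All these dropout rates are assumptions.

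**What the weekly scores can and cannot do.** A second simulation assumed baseline ISI 16 (SD 3), mean improvement 3 (waitlist) and 7 (CBT-I) with SD 4, measurement SD 2, and dropout of about 36% and 12%. All dropouts were given complete weeks 1-5 scores, which is a favourable case. The true week-28 difference is about −4.0.

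| Waitlist dropout driven by | Estimate, baseline only | Estimate, weeks 0-5 |
|---|---|---|
| Improvement visible by week 5 | −5.26 | −4.00 |
| Unobserved later change | −4.75 | −4.76 |

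Only the direction is relied on. Weekly scores remove the bias when they carry the reason for leaving, and do nothing otherwise.

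**Illustrative size of the bias.** Bias ≈ (fraction of waitlist missing) × (how far their true ISI lies below the model's prediction), with no shift in the CBT-I arm. With 20-30% missing and a shift of 2-6 points, it runs from 0.20 × 2 = 0.4 to 0.30 × 6 = 1.8 ISI points. For an assumed SD of 4-5, that is 0.4/5 = 0.08 to 1.8/4 = 0.45 SD, against a design effect of 0.80 SD.

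**The case against.** The strongest defence is that the final condition most naturally refers to nonignorable missingness, the subject of the sentence just before it. Read so, the authors distinguish MAR from MNAR correctly and merely word a limitations paragraph loosely, leaving the method to a fuller plan. The reading is fair, and the choice of method is rightly left there. The condition, however, is stated in this text and is untestable on that reading too.

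A reader might infer more than the documents support on several counts:
- *That the check would stay silent exactly when harm occurs.* Harmful dropout concentrated in the waitlist would tend to show as an arm imbalance, and the paragraph opens with unequal attrition, so arm is a natural variable to examine. The check is weak, not blind.
- *That the article itself describes MNAR dropout.* Leaving after improvement is MNAR only if the model does not see the improvement. Someone who improves by week 6 or 12 and then leaves is covered by the model as written. The article also hedges, and lists loss of interest as another reason.
- *That aim 2 is a ready precedent for weekly data.* Its model lists weeks 0-6, 12 and 28 but names the BDI-II, which Secondary Outcomes does not schedule weekly. It cannot serve as a template.
- *That weekly ISI goes unused.* It feeds the mediation analysis. Aim 1's time points also match the declared primary ones, but keeping those contrasts does not require leaving earlier scores out of the model.
- *That covariates found to predict missingness should be put into the model.* With 49 participants, data-driven selection of that kind is debatable and is not part of this point.

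**Conclusion.** The point holds as a cheap improvement. Whichever way the condition is read, it cannot identify when a sensitivity analysis is needed, and the aim 1 model omits collected scores that are the main post-baseline information on most of those lost. The counts (11 of 49 at week 6, 12 of 49 at week 12) are firm.

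The size of any bias is not established. Attrition by arm at weeks 6-28 is not reported, so the 0.4-1.8 ISI points are illustrative only. They rest on an assumed waitlist missing fraction, an assumed shift and no shift in the CBT-I arm.

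Some of the 11 may have left before week 1 and have no weekly scores: Randomization allows for such losses, and Data Collection counts people as enrolled only once the week 1 questionnaires are done. For them, adding weekly ISI changes nothing. For the others it makes MAR more plausible without assuring it, so it does not replace the MNAR analysis.

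**What to change.** 1. Remove the condition. Always report an MNAR sensitivity analysis for ISI and for the primary depression measure. A delta-adjusted analysis by arm over a prespecified range is one suitable choice.
2. Include the weeks 1-5 ISI scores in the aim 1 mixed model, and keep the treatment contrasts at weeks 6, 12 and 28.
3. Date the change and label it as made after the week-6 interim analyses, which Trial Status and Timeline says had been run. The same section says the primary hypotheses had not yet been tested in full.

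The cost is revised wording, modest extra programming and some added reporting. No new data are needed.

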## Abbreviations

BAI: Beck Anxiety Inventory
BDI-II: Beck Depression Inventory-II
CBT-I: cognitive behavioral therapy for insomnia
CRISIS: Coronavirus Health Impact Survey
DSM-5: Diagnostic and Statistical Manual of Mental Disorders 5th Edition
Duke: Duke Structured Interview for Sleep Disorders
FIRST: Ford Insomnia Response to Stress Test
GAD-7: Generalized Anxiety Disorder-7
ICSD-2: International Classification of Sleep Disorders, 2nd Edition
IPAQ: International Physical Activity Questionnaire
IRB: institutional review board
ISI: Insomnia Severity Index
MAR: missing at random
MCAR: missing completely at random
MINI: Mini-International Neuropsychiatric Interview
PHQ-9: Patient Health Questionnaire-9
PSS: Perceived Stress Scale
SE: sleep efficiency
SF-36: 36-Item Short Form Health Survey
SNI: Social Network Index
SOL: sleep onset latency
S-STS: Sheehan Suicidality Tracking Scale
TST: total sleep time
UCLA: University of California, Los Angeles
WASO: wake after sleep onset
